### Blinding

The blinding method will not be fully suitable for both patients due to the obvious difference in types of intervention between the BC group and the other groups. However, laboratory technicians, ultrasound doctors, and statisticians will be completely blinded. At the same time, this trial will be blinded to recruited patients, the acupuncturists, data collectors, assessors, and statisticians between the other four groups. Patients will be treated in separate rooms or a curtain will be used to cover the bed, while patients will be wearing an eye mask. In the sham acupuncture group, the acupoints will be on the face and the back of limbs, and the operation experience will be consistent with that of acupuncture.

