### Randomization

A random sequence will be generated based on block randomization by an independent research assistant using the software SPSS 26.0. The various eligible participants will be randomly divided into five groups with a 1:1:1:1:1 ratio. The treatment allocation codes will be enclosed by an independent researcher in sequentially numbered opaque envelopes until the first treatment schedule. To minimize coding interruptions, the chief investigator and result evaluators will also turn a blind eye to the treatment allocation.

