### Interventions

The interventions will be combined with the guidelines (3) published by the American Academy of Neurology (AAN) and the American Academy of Otolaryngology-Head and Neck Surgery Foundation (AAO-HNSF) in 2013 and the preliminary experiments of this study (2). Acupuncture will be performed by three different experienced acupuncturists in accordance with STRICTA (19). The subjects in each group, except the blank control group, will receive either acupuncture, electroacupuncture, or sham acupuncture treatment 5 times per week for 4 weeks. Except for the acupuncture control group, patients in each group will receive the following medications. Prednisone acetate tablets will be administered orally at 30 mg per day for 5 days, then it will be reduced by 5 mg per day until discontinued for 10 days (Sinopharm, Rongsheng Pharmaceutical Co. LTD., Jiaozuo, China); Mecobalamin tablets of 0.5 mg will be orally administered, 3 times a day (Eisai (China) Pharmaceutical Co., LTD., Jiaozuo, China); and Vitamin B1 tablets of 10 mg will be administered orally 3 times a day (Fuzhou Haiwang Fuyao Pharmaceutical Co., LTD., Fuzhou, China). During the study, subjects will not be allowed to use traditional Chinese medicine treatment methods other than those prescribed medications to treat the disease (e.g., traditional Chinese medicine preparations, tuina therapy, etc.). The participants can withdraw from the trial for any reason and at any point in time. Researchers can remove participants from the trial with any of the following conditions: (1) the legal representative of the patient requested to withdraw from the study, (2) serious adverse events, and (3) death.

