#### The acupuncture group and the acupuncture control group

The disposable sterile acupuncture needles will be used (0.25 × 40 mm, Suzhou Acupuncture Supplies Co., LTD., China). In all sessions, patients will be treated with eight core acupuncture points and four additional acupoints. The core acupoints will be BL02 (Cuanzhu), GB14 (Yangbai), ST2 (Sibai), SI18 (Quanliao), ST4 (Dicang), ST6 (Jiache), LI4 (Hegu), and LR3 (Taichong), and the additional acupoints can be chosen from the following points: middle ditch askew plus DU26 (Shuigou); nasolabial fold becomes shallow add LI20 (Yingxiang); eyelid closure difficulty plus EX-HN5 (Taiyang); and pain behind the ear mastoid process Ex-HN17 (Yifeng). All acupoints will be carefully selected according to the clinical experience and the literature. After the acupuncture operation, the needle will be retained for 30 min before removal. The treatment will be performed once a day, 5 times as a course of treatment, with 2 days rest among the courses, for a total of 4 courses (weeks). The acupuncture group will be combined with the medicine therapy based on acupuncture treatment. The acupuncture control group will be treated with acupuncture only. The acupuncture points and methods are summarized in Table 2.

**Table 2 tab2:** Acupuncture points and methods.

Acupoint types	Acupuncture point	Direction	Depth (mm)	Electroacupuncture point
Core acupoints	BL02 (Cuazhu, affected side)	Oblique stab in the direction of the eyebrow arch	3–10	No
Core acupoints	GB14 (Yangbai, affected side)	Downward inclined stab	3–10	Yes
Core acupoints	ST2 (Sibai, affected side)	Perpendicular to the skin	3–10	No
Core acupoints	SI18 (Quanliao, affected side)	Perpendicular to the skin	3–10	Yes
Core acupoints	ST4 (Dicang, affected side)	Transversely toward ST6	3–10	Yes
Core acupoints	ST6 (Jiache, affected side)	Transversely toward ST4	3–10	Yes
Core acupoints	LI4 (Hegu, healthy side)	Perpendicular to the skin	3–10	No
Core acupoints	LR3 (Taichong, healthy side)	Perpendicular to the skin	3–10	No
Additional acupoints	DU26 (Shuigou)	Perpendicular to the skin	3–10	No
Additional acupoints	LI20 (Yingxiang, affected side)	Oblique to the nasal root along the nasolabial groove	3–10	No
Additional acupoints	EX-HN5 (Taiyang, affected side)	Lateral epicanthic spur	3–10	No
Additional acupoints	Ex-HN17 (Yifeng, affected side)	Perpendicular to the skin	3–10	No

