#### The electroacupuncture group

The acupuncture points and the treatment course of this group will be the same as those of groups A and AC, and four acupoints will be connected to an electroacupuncture device and treated with electroacupuncture. The needles on GB14 (Yangbai), SI18(Quanliao), ST4 (Dicang), and ST6 (Jiache) will be connected to the SDZ-II Acupuncture Stimulating Instruments (Suzhou Medical Supplies Factory Co., LTD., China) with 2-Hz frequency and the varying amplitude according to the comfort of the participants, ranging from 2 to 5 mA to enhance the sensation of acupuncture. The needles will be kept for 30 min and then removed.

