#### The sham acupuncture group

Patients in this group will be treated with sham acupuncture at the following five non-meridian and non-acupoint stimulation points, and the specific location is shown in Table 3. The location of acupoints can be avoided by referring to the 2006 National Standard of the People’s Republic of China (GB/T 12346-2006) *name and location of acupoints*. Patients will be placed in the supine position, their skin will be disinfected, and the Streitberger placebo needle (0.30 × 30 mm) will be used (24). When the needle is attached to the skin through a plastic ring, the patient might feel a tingling sensation, mimicking a puncture to the skin. However, when the needle is pressed against the skin, it does not penetrate the skin but instead retracts into the handle. The frequency, course, and time of acupuncture will be the same as those of the acupuncture group.

**Table 3 tab3:** The location of stimulation points in the sham acupuncture group.

Stimulation point	Direction	Affected/Healthy side
Stimulation point 1	The midpoint of the line between GB14 (Yangbai) and ST8 (Touwei)	Affected side
Stimulation point 2	The midpoint of the line between ST05 (Daying) and ST4 (Dicang)	Affected side
Stimulation point 3	The midpoint of the line between ST07 (Xiaguan) and SI18 (Quanliao)	Affected side
Stimulation point 4	The midpoint of the connection between the styloid process of the ulna and the olecranon	Healthy side
Stimulation point 5	The midpoint of the line between EX-HN5 (Taiyang) and SP5 (Shangqiu)	Healthy side

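### Blinding of patients and acupuncturists across the four needled arms is claimed but not achievable, and two sections disagree on whether primary-outcome raters are blind to the medicine-only arm

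*Protocol article*

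**What the plan says.** The Blinding section of the protocol article concedes that BC cannot be fully masked. It then names one group of staff without restriction: "laboratory technicians, ultrasound doctors, and statisticians will be completely blinded". For EA, A, SA and AC it says that "this trial will be blinded to recruited patients, the acupuncturists, data collectors, assessors, and statisticians between the other four groups". The means given are separate rooms or a curtain, and an eye mask. The Discussion repeats the aim of full blindness in these four arms by the same means.

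The Randomization section adds, with no exception for BC, that "the chief investigator and result evaluators will also turn a blind eye to the treatment allocation".

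The intervention sections describe what each arm receives:

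- **Tablets.** "Except for the acupuncture control group, patients in each group will receive the following medications". The section on A and AC confirms it: "The acupuncture control group will be treated with acupuncture only". No placebo tablets are described.
- **Current.** In EA, four of the needles are wired to a stimulator with "varying amplitude according to the comfort of the participants, ranging from 2 to 5 mA to enhance the sensation of acupuncture". No dummy stimulation is described for the other arms.
- **Sham.** SA patients are "treated with sham acupuncture at the following five non-meridian and non-acupoint stimulation points", with a retracting, non-penetrating needle.

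**The concern.** Blinding between two arms requires that the person in question cannot tell them apart from what they do, receive or see. The arms here differ in features that the operator handles directly and, for most pairs, that the patient experiences directly. The stated masking measures address neither.

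The primary outcome is the day-20 effectiveness rate, built from HBGS and SFGS (Table 4). A person scores both by judging the face. If the trial is reported as four mutually blinded arms, differences that include patient expectation and operator behaviour could be read as specific effects of needling or current. If the raters are not blind to BC, the four comparisons with medicine alone lose their main protection against biased scoring. The ultrasound and laboratory outcomes do not share this second problem, because the staff who measure them are named as completely blinded.

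**Working it through.** The plan gives no figure for this point, so the check sets the sections side by side and counts pairs.

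**Inputs**

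- Needling in A and AC: the same 0.25 × 40 mm needles, eight core points plus additional ones from a list of four, depth 3–10 mm, 30 min retention, same schedule (section on A and AC, Table 2). The two arms differ only in tablets.
- Needling in EA: the same points and course, with four needles wired and the current adjusted between 2 and 5 mA (electroacupuncture section).
- Needling in SA: 0.30 × 30 mm retracting needle at five other locations (sham section, Table 3).
- Tablets: given in EA, A, SA and BC, not in AC (Interventions).

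**Pairs.** Five arms give 5 × 4 / 2 = 10 pairs. Four involve BC, for which the protocol already concedes limited blinding. The four needled arms give 4 × 3 / 2 = 6 pairs.

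| Pair | Can the acupuncturist be blind? | Can the patient be blind? |
|---|---|---|
| EA vs A | No: stimulator | Unlikely: felt current |
| EA vs SA | No: stimulator, needle, points | Unlikely: felt current |
| EA vs AC | No: stimulator | No: tablets |
| A vs SA | No: needle, points | Plausibly |
| SA vs AC | No: needle, points | No: tablets |
| A vs AC | Possibly, if tablets are not disclosed | No: tablets |

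- Acupuncturist: 5 of 6 pairs fail, namely every pair containing EA or SA. One (A vs AC) is feasible.
- Patient: 3 pairs fail on tablets and 2 more on the current, so 3 + 2 = 5 of 6. One (A vs SA) is plausible, although it still differs in number of points and in penetration.
- The one pair feasible for the operator is not the one plausible for the patient. On the design described, no pair can be blind for both.

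**Masking measures against cues.** An eye mask, curtain or separate room hides neither the sensation of current nor the absence of tablets, and hides nothing from the person inserting the needles. The blinding-success check at day 20 in Table 1 measures masking; it does not create it.

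**Raters.** The Randomization section makes result evaluators blind to allocation without exception. The Blinding section leaves assessors out of the completely blinded list and names them only in the sentence limited to the four needled arms. Read literally, the two sections differ on exactly the four pairs that involve BC.

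**The case against.** The strongest reply concerns the raters. Statisticians appear both in the completely blinded list and in the four-arm sentence, so being named in the second does not imply being unblinded to BC. Together with the Randomization section, the natural reading may be that assessors are blind throughout. This stands to the extent that a reader might infer that the primary raters know who is in BC, and the documents do not support that. They show two statements that do not match and need reconciling.

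A reader might also infer that no pair can be operator-blinded. That goes too far: A and AC share identical needling.

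It is tempting to call every comparison other than A vs SA open-label. With blinded raters they would be assessor-blinded with unblinded patients, which is a different and better position.

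Nor does the protocol say that EA vs AC or AC vs SA will be reported as placebo-controlled; the Discussion assigns the placebo question to the sham arm. The risk comes from the blanket blinding claim, not from a stated analysis.

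Finally, a felt current reveals the arm only to patients who know that other arms have none, and the information given to patients is not available here. This softens the two EA rows decided by current. It does not affect the tablet cue in AC or the position of the acupuncturist.

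**Conclusion.** The claim of blinding for patients and acupuncturists across EA, A, SA and AC is wrong as written, because the article's own intervention sections rule it out. Five of the six pairs cannot be operator-blinded. Three of six are disclosed to patients by tablets, and two more probably by current. Only A vs SA can plausibly separate a specific needling effect from patient expectation, and there the operator is unblinded.

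This assumes that no placebo tablets and no dummy stimulation exist beyond what the article describes. The EA rows further assume that patients know in general terms what the other arms receive.

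The rater point is narrower: an inconsistency between the Randomization and Blinding sections, not evidence that raters are unblinded. It still matters because it concerns the people who score the primary outcome. The whole point should be corrected, but it does not undermine randomization, the endpoint or the sample size.

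**What to change.** 1. Restate blinding by role and by pair in the Blinding section and the Discussion: acupuncturists not blinded, except possibly A vs AC; patients blinded for A vs SA only.
2. Reconcile the Randomization and Blinding sections so that the HBGS/SFGS assessors already planned take no part in needling and are blind to all five arms, alongside the ultrasound, laboratory and statistical staff.
3. Describe the other comparisons as assessor-blinded with unblinded patients, and limit conclusions about an effect beyond placebo to A vs SA.
4. Keep the day-20 blinding-success check in all needled arms and report it by arm. That is how failed masking in EA or AC would show.

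The cost is protocol wording and an instruction to existing assessors. The downside is a weaker but accurate blinding claim. Recruitment began in October 2021 and is scheduled to the end of 2025, so the rater arrangement should be settled promptly; independence cannot be restored for ratings already made.

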### Interventions

The interventions will be combined with the guidelines (3) published by the American Academy of Neurology (AAN) and the American Academy of Otolaryngology-Head and Neck Surgery Foundation (AAO-HNSF) in 2013 and the preliminary experiments of this study (2). Acupuncture will be performed by three different experienced acupuncturists in accordance with STRICTA (19). The subjects in each group, except the blank control group, will receive either acupuncture, electroacupuncture, or sham acupuncture treatment 5 times per week for 4 weeks. Except for the acupuncture control group, patients in each group will receive the following medications. Prednisone acetate tablets will be administered orally at 30 mg per day for 5 days, then it will be reduced by 5 mg per day until discontinued for 10 days (Sinopharm, Rongsheng Pharmaceutical Co. LTD., Jiaozuo, China); Mecobalamin tablets of 0.5 mg will be orally administered, 3 times a day (Eisai (China) Pharmaceutical Co., LTD., Jiaozuo, China); and Vitamin B1 tablets of 10 mg will be administered orally 3 times a day (Fuzhou Haiwang Fuyao Pharmaceutical Co., LTD., Fuzhou, China). During the study, subjects will not be allowed to use traditional Chinese medicine treatment methods other than those prescribed medications to treat the disease (e.g., traditional Chinese medicine preparations, tuina therapy, etc.). The participants can withdraw from the trial for any reason and at any point in time. Researchers can remove participants from the trial with any of the following conditions: (1) the legal representative of the patient requested to withdraw from the study, (2) serious adverse events, and (3) death.

#### The acupuncture group and the acupuncture control group

The disposable sterile acupuncture needles will be used (0.25 × 40 mm, Suzhou Acupuncture Supplies Co., LTD., China). In all sessions, patients will be treated with eight core acupuncture points and four additional acupoints. The core acupoints will be BL02 (Cuanzhu), GB14 (Yangbai), ST2 (Sibai), SI18 (Quanliao), ST4 (Dicang), ST6 (Jiache), LI4 (Hegu), and LR3 (Taichong), and the additional acupoints can be chosen from the following points: middle ditch askew plus DU26 (Shuigou); nasolabial fold becomes shallow add LI20 (Yingxiang); eyelid closure difficulty plus EX-HN5 (Taiyang); and pain behind the ear mastoid process Ex-HN17 (Yifeng). All acupoints will be carefully selected according to the clinical experience and the literature. After the acupuncture operation, the needle will be retained for 30 min before removal. The treatment will be performed once a day, 5 times as a course of treatment, with 2 days rest among the courses, for a total of 4 courses (weeks). The acupuncture group will be combined with the medicine therapy based on acupuncture treatment. The acupuncture control group will be treated with acupuncture only. The acupuncture points and methods are summarized in Table 2.

**Table 2 tab2:** Acupuncture points and methods.

Acupoint types	Acupuncture point	Direction	Depth (mm)	Electroacupuncture point
Core acupoints	BL02 (Cuazhu, affected side)	Oblique stab in the direction of the eyebrow arch	3–10	No
Core acupoints	GB14 (Yangbai, affected side)	Downward inclined stab	3–10	Yes
Core acupoints	ST2 (Sibai, affected side)	Perpendicular to the skin	3–10	No
Core acupoints	SI18 (Quanliao, affected side)	Perpendicular to the skin	3–10	Yes
Core acupoints	ST4 (Dicang, affected side)	Transversely toward ST6	3–10	Yes
Core acupoints	ST6 (Jiache, affected side)	Transversely toward ST4	3–10	Yes
Core acupoints	LI4 (Hegu, healthy side)	Perpendicular to the skin	3–10	No
Core acupoints	LR3 (Taichong, healthy side)	Perpendicular to the skin	3–10	No
Additional acupoints	DU26 (Shuigou)	Perpendicular to the skin	3–10	No
Additional acupoints	LI20 (Yingxiang, affected side)	Oblique to the nasal root along the nasolabial groove	3–10	No
Additional acupoints	EX-HN5 (Taiyang, affected side)	Lateral epicanthic spur	3–10	No
Additional acupoints	Ex-HN17 (Yifeng, affected side)	Perpendicular to the skin	3–10	No

#### The electroacupuncture group

The acupuncture points and the treatment course of this group will be the same as those of groups A and AC, and four acupoints will be connected to an electroacupuncture device and treated with electroacupuncture. The needles on GB14 (Yangbai), SI18(Quanliao), ST4 (Dicang), and ST6 (Jiache) will be connected to the SDZ-II Acupuncture Stimulating Instruments (Suzhou Medical Supplies Factory Co., LTD., China) with 2-Hz frequency and the varying amplitude according to the comfort of the participants, ranging from 2 to 5 mA to enhance the sensation of acupuncture. The needles will be kept for 30 min and then removed.

#### The sham acupuncture group

Patients in this group will be treated with sham acupuncture at the following five non-meridian and non-acupoint stimulation points, and the specific location is shown in Table 3. The location of acupoints can be avoided by referring to the 2006 National Standard of the People’s Republic of China (GB/T 12346-2006) *name and location of acupoints*. Patients will be placed in the supine position, their skin will be disinfected, and the Streitberger placebo needle (0.30 × 30 mm) will be used (24). When the needle is attached to the skin through a plastic ring, the patient might feel a tingling sensation, mimicking a puncture to the skin. However, when the needle is pressed against the skin, it does not penetrate the skin but instead retracts into the handle. The frequency, course, and time of acupuncture will be the same as those of the acupuncture group.

**Table 3 tab3:** The location of stimulation points in the sham acupuncture group.

Stimulation point	Direction	Affected/Healthy side
Stimulation point 1	The midpoint of the line between GB14 (Yangbai) and ST8 (Touwei)	Affected side
Stimulation point 2	The midpoint of the line between ST05 (Daying) and ST4 (Dicang)	Affected side
Stimulation point 3	The midpoint of the line between ST07 (Xiaguan) and SI18 (Quanliao)	Affected side
Stimulation point 4	The midpoint of the connection between the styloid process of the ulna and the olecranon	Healthy side
Stimulation point 5	The midpoint of the line between EX-HN5 (Taiyang) and SP5 (Shangqiu)	Healthy side

#### The blank control group

Except for the medicine therapy, no electropuncture, acupuncture, or sham acupuncture will be carried out during the whole experiment in this group.

### Outcome measures

The outcome evaluation will be conducted at 6 time points, including the baseline, days 5, 10, and 20, and weeks 8 and 12 of treatment. In addition, SFGS and HBGS will be evaluated before each treatment to evaluate the recovery rate. Safety measures will be assessed at the baseline and day 20 of the treatment. The evaluation schedule is shown in Table 1.

#### Primary outcome measures

The primary outcome is the effectiveness rate after the intervention period, which will be evaluated immediately at the end of treatment on the 20th day. Combined with the results of SFGS and HBGS, the efficacy evaluation criteria have been formulated according to the *Evaluation and efficacy standard of Integrated Chinese and Western Medicine for peripheral facial nerve palsy (draft)* by Yang et al. (25) as shown in Table 4. The effectiveness rate is calculated by dividing the sum of the number of cured, efficacious, and effective patients in each group by the number of patients in each group. The Sunnybrook facial grading system (SFGS) is composed of three distinct areas that generate a comprehensive score describing the overall static and dynamic state of the face. Final score = free movement points – static points – linkage points. SFGS score can range between 0 and 100, and the higher the score is, the better facial nerve function (26). The House-Brackmann facial nerve grading system (HBGS) is a scale for assessing the severity of Bell’s palsy, which can potentially classify facial nerve injury into six grades (27). Grade I indicates normal function, grade II mild dysfunction, grade ≤ IV moderate palsy, and grade ≥ V severe palsy (27). SFGS and HBGS scores will be evaluated prior to each treatment until the end of the study and during the follow-up periods of 8 and 12 weeks of treatment.

Recovery speed: the patient’s recovery will be evaluated daily through SFGS and HBGS until the patient is assessed as “cure” according to the evaluation criteria for curative effect (Table 4). The period from baseline to this time is considered the recovery time. If the patient’s recovery time is shorter, it will be considered that the recovery speed is faster.The diameter of the facial nerve: bilateral nerve color Doppler ultrasonography will be conducted by a board-certified neurosonologist in the Department of Ultrasound of CMU1H. The diameter of the main trunk and five branches of the facial nerve on both sides of the face will be measured three times, and the average value will be taken.Echo intensity and thickness of facial muscles: the thickness and recovery strength of the frontalis muscle, the orbicularis oculi muscle, the orbicularis oris muscle, the depressor anguli oris muscle, the depressor labii inferioris, and the mentalis muscle will be measured using a diagnostic ultrasound system. The determination of maximum muscle thickness has been reported to be orthogonal to the direction of muscle fibers (19). Thus, gray analysis will be used to quantify the echo intensity of each muscle (19). The results of three independent measurements for each muscle will be averaged to minimize the differences.Blood flow parameters of facial artery: color Doppler ultrasound will be used to measure and record the systolic peak velocity (Vs), end-diastolic velocity (Vd), and resistance index (RI) of bilateral facial artery, inferior labial artery, and superior labial artery. All data will be measured three times and thereafter averaged.The serum inflammatory level: at the baseline; 5, 10, and 20 days of treatment; 8 and 12 weeks of treatment; the count of neutrophils, lymphocytes, platelets; and the levels of interleukin-6 (IL-6), interleukin-8 (IL-8), interleukin-10 (IL-10), and tumor necrosis factor-α (TNF-α) will be measured to assess the levels of immune inflammation.Safety evaluation: the various safety indicators will be measured at the baseline and the end of treatment, including blood routine (the count of neutrophils, lymphocytes, platelets, monocytes, and hemoglobin content), the liver function (alanine aminotransferase and aspartate aminotransferase), and the kidney function (blood urea nitrogen and serum creatinine).Adverse events: acupuncture can exhibit potential adverse events, such as pain, hematoma, and infection, and the participants will be clearly informed about all these adverse events before signing informed consent. We will also provide appropriate medical care for the commonly observed adverse reactions. Any adverse events will be recorded by CRF. In case of serious adverse events, treatment will be terminated, and a detailed report will be made to researchers and the ethics committee within 24 h of the occurrence. The ethics committee will make recommendations and decide whether the patient can continue the treatment. We will give them proper compensation for their medical expenses.

**Table 4 tab4:** Evaluation criteria for curative effects.

Curative effect	HBGS	SFGS
Cure	Grade I	≥ 90
Efficacious	Grade II	70–89
Effective	Grade III	50–69
Ineffective	Grade IV and above	< 50

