**Figure 1 fig1:**
[figure not shown]
Flow chart of the planned study. EA: electroacupuncture; A: acupuncture; SA: sham acupuncture; BC: blank control; and AC: acupuncture control.

**Table 1 tab1:** The designed schedule for the data collection.

Time point	Screening period	Intervention period					Follow-up period	
	Day 0	Day1	Day 5 (Week1)	Day 10 (Week2)	Day 20 (Week4)	Once daily until discharge	Week 8 ± 3 days	Week 12 ± 3 days
Enrolment								
Informed consent	×							
Eligibility screening	×							
Randomization	×							
Allocation	×							
Interventions								
The electroacupuncture group								
The acupuncture group								
The sham acupuncture group								
The blank control group								
The acupuncture control group								
Assessments								
SFGS	×		×	×	×	×	×	×
HBGS	×		×	×	×	×	×	×
The diameter of facial nerve	×		×	×	×		×	×
Echo intensity and thickness of facial muscles	×		×	×	×		×	×
Blood flow parameters of the facial artery	×		×	×	×		×	×
Therapeutic mechanism index	×		×	×	×		×	×
Safety index	×		×	×	×			
Adverse events			×	×	×	×		
Success of blinding					×			

The treatment course will last for 20 days (4 weeks) and thereafter follow up for 8 weeks. First, the subjects will be informed of informed consent and screening. Then, they will be randomized into five different groups. The four groups related to acupuncture will be treated with acupuncture 5 times a week for a total of 4 weeks (20 days); the blank control group will receive the medicine therapy (see “Intervention” for details). The clinical data will be evaluated at baseline, days 5, 10, and 20 (weeks 1, 2, and 4), and weeks 8 and 12 of treatment. The Sunnybrook facial grading system (SFGS), the House-Brackmann facial nerve grading system (HBGS), and adverse events will be evaluated daily during treatment. During treatment, adverse events will be recorded in the Case Report Form (CRF) at any time.

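### The ratings behind recovery speed have conflicting schedules and stopping points, and a single unconfirmed cure rating fixes the recovery date.

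*Protocol article*

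**What the plan says.** Recovery speed is the first secondary outcome listed in the abstract. The protocol article gives several rules for the SFGS and HBGS ratings it depends on.

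- **Recovery-speed item (outcome list, after the primary outcome):** "recovery will be evaluated daily through SFGS and HBGS until the patient is assessed as" cured under Table 4. Then: "The period from baseline to this time is considered the recovery time".
- **Table 1, column heading:** "Once daily until discharge", with both scales marked in that column.
- **Note to Table 1:** the two scales and adverse events "will be evaluated daily during treatment".
- **Outcome measures:** "SFGS and HBGS will be evaluated before each treatment to evaluate the recovery rate".
- **Primary outcome measures:** "SFGS and HBGS scores will be evaluated prior to each treatment until the end of the study and during the follow-up periods" at weeks 8 and 12.

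Sessions take place five times a week for four weeks with two rest days between courses (section on the acupuncture and acupuncture control groups). The blank control group receives medication only. Table 4 sets cure at HBGS Grade I and SFGS of at least 90. Apart from the daily ratings, fixed visits take place at baseline, days 5, 10 and 20, and weeks 8 and 12.

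**The concern.** Recovery time can be no more exact than the days on which a patient is rated. If staff follow different sections, patients with the same course get different recovery dates. If the rule is tied to treatment sessions, one arm has no sessions to tie it to. A difference in rating days between arms could then pass for a difference in recovery speed.

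The definition is also fragile. The first rating that meets cure is the event, nothing has to confirm it, and under the recovery-speed item daily rating ends there. A patient who falls back the next day keeps the early date, and the relapse is seen only at the next fixed visit. By contrast, the ultrasound measurements are each taken three times and averaged.

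**Working it through.** **Step 1: the rules side by side.**

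| Place | Frequency | Stops at |
|---|---|---|
| Recovery-speed item | daily | first cure |
| Table 1 column | once daily | discharge |
| Table 1 note | daily | end of treatment |
| Outcome measures | before each treatment | not stated |
| Primary outcome measures | before each treatment | end of study, plus weeks 8 and 12 |

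Both frequency and stopping point differ. Before each treatment means 5 × 4 = 20 ratings in the acupuncture arms and no defined number under blank control. If daily medication is counted as treatment there, that arm's rating days differ from the other arms'.

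**Step 2: calendar gaps under session-only rating.** The last session falls on calendar day 20 + 3 × 2 = 26. Week 8 is day 56, so the gap is 30 days (visit window ±3). A patient who first meets cure on day 27 would be dated at day 56, 29 days late.

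**Step 3: chance of a false cure.** The documents state no figure to reproduce and give no rating error, so everything from here on is an assumption. With a chance q of a false cure at each rating and independent ratings, P(at least one in k) = 1 − (1 − q)^k.

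- q = 1%, 2%, 5%, with k = 10: 10%, 18%, 40%.
- The same q, with k = 20: 18%, 33%, 64%.

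For a patient with a stable true SFGS of 85, using SFGS alone and counting 89.5 or more as 90, q = P(Z > 4.5/SD):

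| Error SD | q | At least one cure in 10 ratings | Two consecutive |
|---|---|---|---|
| 2 | 1.2% | 12% | 0.1% |
| 3 | 6.7% | 50% | 4% |
| 4 | 13.0% | 75% | 13% |

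If errors on the same patient are correlated at 0.5 or 0.8 (also assumed), the single-rating figure at SD 4 falls to 48% or 32%. At SD 3 it falls to about 30% or 19%. The two-consecutive rule then does less well: about 17% to 18% at SD 4 and 8% to 9% at SD 3.

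**Step 4: direction of the dating error.** Simulated patients start at SFGS 50 and gain a median of 1, 2 or 3 points a day (log-SD 0.3), with independent error. Cure is a rated SFGS of at least 90, and HBGS is not modelled. Entries are the mean error in days against the true crossing day, for median gains of 1 / 2 / 3 points a day (negative = early).

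| Error SD | Every day, first cure | Every day, two consecutive | Sessions then weeks 8 and 12, first cure |
|---|---|---|---|
| 0 | 0 / 0 / 0 | 0 / 0 / 0 | +15.1 / +5.0 / +0.7 |
| 2 | −1.1 / −0.3 / −0.1 | +0.2 / +0.2 / +0.1 | +14.8 / +4.5 / +0.7 |
| 4 | −3.5 / −1.1 / −0.5 | −0.2 / +0.2 / +0.2 | +14.0 / +3.0 / +0.2 |
| 6 | −6.4 / −2.3 / −1.1 | −1.0 / +0.1 / +0.2 | +12.5 / +1.4 / −0.4 |

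Rating every day with a single cure gives early dates whenever there is error, and exact dates when there is none. Session-only rating gives mostly late dates. The sign of the error therefore depends on which section is followed.

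**The case against.** A reader might infer that recovery will always be dated too early. The documents do not support this. They give no rating error; with exact ratings and daily assessment the shift is zero; and with session-only rating it is mostly late. A reader might also infer that one SFGS point separates an entrant scoring 89 from the event. That holds only if SFGS decides alone. Table 4 pairs the score with Grade I, the primary-outcome text and the discussion describe the two scales as combined, and entry requires Grade II or worse. A joint requirement would reduce the percentages above, as would correlated errors.

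It can also be said that discharge in Table 1 means the end of treatment, since the column lies under the intervention period and the note says daily during treatment. That is plausible, so a loss of data tied to ward or outpatient care is possible but not established. Likewise, the recovery-speed item may define only the event, while other sections govern data collection. On that reading later ratings are not lost, and the fixed visits continue on any reading. Assessors are meant to be blinded, and no bias between arms is demonstrated.

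What stands is that these readings have to be chosen by the reader. None of them settles daily against before each treatment, none supplies a session-based schedule for blank control, and none adds a confirmation of cure. Reconciling the stopping point alone would leave the single-rating definition in place.

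**Conclusion.** The contradiction is in the text and needs no assumption: the ratings that define recovery speed have incompatible frequencies and stopping points, and the session-based wording does not fit one of the five arms. The single unconfirmed rating is a real weakness, but early dating is a risk rather than a demonstrated bias. Its size is unknown; 0.1 to 6.4 days is illustrative and rests on assumed SDs of 2 to 6, independent errors, SFGS alone and rating every day. Session-only rating could shift dates late, by up to about 15 days on average in the slowest-recovery scenario. The effect is confined to a secondary outcome, because the primary outcome is read at day 20. The plan should be corrected, but this does not threaten the main result.

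**What to change.** 1. Reconcile Table 1 and its note, Outcome measures, Primary outcome measures and the recovery-speed item to one schedule. Name the same rating days for all five arms through day 20, including blank control, and continue them whatever the cure or discharge status. Remove first cure and discharge as stopping points for rating.
2. Define the recovery date as the first of two consecutive scheduled ratings that meet cure, and say explicitly whether both scales must meet Table 4. A first cure at the last treatment-period rating is confirmed at the next scheduled visit. State how a first cure at week 12, which has no later visit, is counted.
3. Keep the date of the first single cure rating as a sensitivity analysis.

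The cost is a few sentences and one column heading. The daily wording already implies these ratings, although blank control patients must be rated on the named days. Recovery dates become slightly later, and a few confirmations wait until week 8. The gap between day 20 and week 8 remains, so later recoveries are still dated coarsely, but on the same schedule in every arm. No treatment rule changes.
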